### Data management

The study steering committee determined that a data monitoring committee was unnecessary for this study, as it poses a minimal risk to patient safety and uses only routinely collected or patient-reported data.

#### Patient-reported outcome measure data

Participants will complete PROMS using PROFILES (Patient-Reported Outcomes Following Initial treatment and Long-term Evaluation of Survivorship), an online PROM collection and data management system developed in the Netherlands and implemented at the Royal Marsden [44]. Follow-up time points will be managed by the Royal Marsden as the coordinating center. PROM responses cannot be viewed by the researcher or clinical team until extracted at the end of the study when it will be linked to other study data by the study identification number.

#### Clinical data

With patient informed consent, researchers will collect relevant clinical data from the local electronic patient record and store it digitally at the Royal Marsden. Clinical data will be extracted at the end of the study and linked to other study data by the study identification number.

#### Health care utilization

Study participants will be identified in Discover by NHS number and flagged with the study identification number. The Imperial College Health Partners Discover team will access a de-identified version of the data to analyze health and social care resource utilization on behalf of the Royal Marsden. Health and social care resource utilization data will be extracted at the end of the study and linked to other study data by the study identification number.

#### OWise engagement

Participants will be provided with a unique invitation code linked to their study identification number to input when creating an OWise account. Timestamp data will be identified by the invitation code and extracted at the end of the study. The data will be linked to other study data by the unique invitation code.

### Sample size

Sample size calculations are based on the change in PAM-13 score from baseline to 3 months. A difference of four points is considered clinically relevant [29, 45]. In a similar study, the mean PAM-13 score at baseline for the intervention group was 61.3 (SD 16.61) and 67.9 (SD 16.85) at 3 months [46]. For the control group, the study reported a mean PAM-13 score at baseline of 62.1 (SD 17.30) and 62.8 (SD 14.94) at 3 months. Based on these findings, this study is planned to detect a mean change difference of 5.90 assuming a common standard deviation of 10.0. Using an 80% power, the study will recruit 47 patients per group. This was calculated using a two-sided test with alpha = 0.05. We will increase the sample size taking 23% attrition at 3 months into account (47/(1–0.23)) to 61 patients per group [47] and, as mentioned above, increase the sample size accordingly if contamination is found near the end of recruitment.

### Analysis

The CONSORT-EHEALTH recommendations for reporting randomized trials for developing and evaluating eHealth interventions will guide trial reports [48]. Primary and secondary outcomes will be assessed using intention-to-treat analysis where all participants are analyzed according to the arm to which they were randomized. We will conduct a sensitivity analysis separately as described below. The data will be analyzed after all patients have completed the 1-year follow-up. Data will be reported descriptively at each time point. Mean and standard deviation or median and range will be reported for continuous outcomes. Frequency and percentage will be reported for categorical outcomes.

The association between potential covariates and the primary and secondary endpoints will be explored using univariate analysis. Any variables with a *p* value of < 0.1 will be included in the multivariable model. Multivariable analysis controlling for potential covariates associated with the particular outcome will be conducted using logistic regression for binary outcomes and multiple linear regression for continuous outcomes. Two-sided *p* values of < 0.05 will be considered statistically significant.

#### Primary endpoint

We will compare the PAM-13 score change between the intervention arm and the control arm using independent *t* test. Data will be log-transformed to achieve normality as appropriate. We will also compare the mean change in PAM-13 score in the intervention and control arm in a multiple linear regression model including potential covariates.

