### Randomization

Patients will be randomly assigned (1:1) to the intervention or control group [19, 20]. Randomization will be stratified by age group and center. Age is grouped by (1) under 60 years old and (2) 60 years old and over as internet access drops between age groups 45–55 and 55–65 [21] and the incidence of breast cancer in the UK is evenly distributed around age 60 [1]. The Institute of Cancer Research Clinical Trials and Statistics Unit Randomisation Service will generate the randomization sequence and allocate the group by phone.

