### Secondary objectives

To test whether any difference in the change in patient activation between the two groups still exists after controlling for potential covariates.To test whether the use of OWise leads to a smaller decrease in health status at 3-month follow-up than standard care after controlling for potential covariates.To test whether the use of OWise leads to a smaller decrease in HRQoL at 3-month follow-up than standard care alone after controlling for potential covariates.To test whether the use of OWise leads to a lower increase in psychological distress at 3-month follow-up compared to standard care alone after controlling for potential covariates.To test whether the use of OWise reduces the rate of resource utilization in the first year following diagnosis compared to standard care among patients registered in Discover, an integrated health and social care record in North West London.To test whether the use of OWise reduces the average cost per patient in the first year following diagnosis compared to standard care among patients registered in Discover.To describe the change in patient activation in the intervention group compared to the control group in the first year following diagnosis.To describe the level of OWise uptake in the intervention group in the first year following diagnosis.To describe the change in the pattern of patient activation, HRQoL, psychological distress, and health status in the intervention group compared to the control group in the first year following diagnosis.

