#### Secondary endpoints

We will compare the mean change in EQ-5D-5L index score and visual analogue score, EORTC QLQ-C30 and EORTC QLQ-BR45 scale scores in the intervention and control arm in simple and multiple linear regression models including potential covariates.

We will compare the mean change in the three HADS scale scores in the intervention and control arm in simple and multiple linear regression models including potential covariates. Based on the continuous overall psychological distress score, patients are classified as ‘distressed’ when they have a score of ≥ 8, and ‘not distressed’ when they have a score < 8. Frequency, percentages, and any appropriate 95% confidence intervals of this dichotomization at baseline and 3 months will be presented. Chi-square or Fisher’s exact test will be used to compare the level of distress between the intervention and control arms.

We will present the mean rate of resource utilization and cost per patient in the two groups by type of resource (primary, secondary and social care) and for total NHS resources used. Simple and multiple linear regression models including potential covariates will compare the mean rate of total resource utilization and the mean cost per patient in the two groups.

We will describe the average scale scores of the four validated measures in the two groups at the four time points and show graphically the trend in scale scores in each group. We will also compare the mean change in scale scores of the measures across the four time points between the intervention and control arm using a mixed models approach.

To describe OWise uptake, the average number of times logging in at daily intervals throughout the follow-up period will be described and the trend of mean logging in over time will be graphed. We will also show the average frequency of use for each function of the tool over time.

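### Free gain in precision: pre-specify baseline PAM-13, age group and centre in the primary model instead of an unadjusted t test on change

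*Protocol article*

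**What the plan says.** - **Primary test** (Protocol article, Primary endpoint): "We will compare the PAM-13 score change between the intervention arm and the control arm using independent" *t* test. The same section adds a comparison of mean change "in a multiple linear regression model including potential covariates".
- **Status of that regression** (Secondary objectives): it serves the first secondary objective, "To test whether any difference in the change in patient activation between the two groups still exists after controlling for potential covariates".
- **Choice of covariates** (Analysis): variables with a univariate p value below 0.1 "will be included in the multivariable model". The article names no covariate that is always included.
- **Randomisation** (Randomization): "Patients will be randomly assigned (1:1) to the intervention or control group", and "Randomization will be stratified by age group and center". Age is split at 60.
- **Planning** (Sample size): "Sample size calculations are based on the change in PAM-13 score from baseline to 3 months". The assumptions are a difference of 5.90, a common SD of 10.0, 80% power and two-sided alpha 0.05, giving 47 per group and 61 after 23% attrition.
- **Secondary questionnaires** (Secondary endpoints): these use the same change-score form, for example "We will compare the mean change in the three HADS scale scores in the intervention and control arm in simple and multiple linear regression models". EQ-5D-5L and the EORTC scales are handled likewise.

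**The concern.** Two things known before treatment starts, the participant's own baseline PAM-13 and her randomisation stratum, are not used efficiently in the primary test.

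First, change is follow-up minus 1 × baseline. Unless the regression slope of follow-up on baseline really is 1, this over-corrects. A group that happens to start higher is then expected to show a smaller change with no treatment effect at all, and the estimated difference moves with that chance imbalance.

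Second, stratifying balances the arms on age group and centre. A two-sample *t* test does not credit that balance, so its standard error tends to be somewhat too large.

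The planned regression does not settle the matter. It is secondary, and its covariates are chosen from the trial data by a significance screen. In a trial planned on 94 evaluable participants, with four points taken as the clinically relevant difference, even a modest gain in precision is worth having when it costs nothing.

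**Working it through.** **Inputs** (all from Sample size). Difference 5.90; SD of change 10.0; 47 per group. PAM-13 SDs in the similar study: intervention 16.61 at baseline and 16.85 at 3 months; control 17.30 and 14.94.

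**1. The plan's figure.** The two-sample *t* calculation with 5.90/10.0 = 0.59 gives 46.08, so 47 per group, as stated. 47/0.77 = 61.04, against 61 stated. Power at 47 per group is 0.808.

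**2. Correlation and slope implied by the plan.**
- Pooled SDs: s0 = √((16.61² + 17.30²)/2) = 16.96; s1 = √((16.85² + 14.94²)/2) = 15.92.
- From SD_change² = s0² + s1² − 2·r·s0·s1, with SD_change = 10.0: r = 0.817.
- Slope of follow-up on baseline = r·s1/s0 = 0.767.

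**3. Error variance under ANCOVA.** Residual variance is s1²(1 − r²).
- Pooled SDs: residual SD = 15.92 × √(1 − 0.817²) = 9.19; ratio to the change-score variance 0.84.
- Averaging the variances of the two cited arms instead: ratio 0.83.
- If the SDs at the two times are equal: ratio (1 + r)/2 = 0.91, residual SD 9.53.

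The reduction is therefore about 9% to 17%. Part of the upper figure comes from the fall in the control-arm SD, 17.30 to 14.94, in one cited study.

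**4. Power at 47 per group, noncentral *t*.**

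| Analysis | Residual SD | Power at 5.9 points | Power at 4 points |
|---|---|---|---|
| *t* test on change | 10.0 | 0.81 | 0.48 |
| ANCOVA, equal SDs | 9.53 | 0.84 | 0.52 |
| ANCOVA, quoted SDs | 9.19 | 0.87 | 0.55 |

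With the quoted SDs the standard error falls from 10.0 × √(2/47) = 2.06 to 9.19 × √(2/47) = 1.89. A simulation of 10,000 trials gave power of 0.81 and 0.87.

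**5. Chance imbalance.** For each point by which the intervention arm starts higher, the change-score estimate moves by 0.767 − 1 = −0.23. One SD of chance imbalance is 16.96 × √(2/47) = 3.5 points, which moves it by about −0.8. Over repeated randomisation both estimators averaged 5.90 for a true 5.90. Their correlations with the imbalance were −0.40 (change score) and 0.00 (ANCOVA).

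**6. Other correlations (assumed, not in the document).** Keeping the quoted SDs, power for 5.9 points goes from 0.60 to 0.70 at r = 0.7 and from about 0.40 to 0.54 at r = 0.5. These rows imply SDs of change of 12.77 and 16.47, not 10.0.

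**7. Strata.** The document gives no figure for how far PAM-13 varies by age group or centre, so their added gain cannot be computed.

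**The case against.** The defence is substantial. The test is pre-specified, valid, and matches the basis of the sample size, which reproduces. A change score does use the baseline, so a reader who infers that baseline PAM-13 is ignored goes too far: it is used with a fixed slope. Nor is the *t* test biased by baseline imbalance; over randomisation it is unbiased, and ANCOVA removes only the conditional error from imbalance that arose by chance. Omitting the strata tends to make the test conservative; it does not bias the estimate or inflate type I error. All of this stands.

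Adjustment is also partly planned. Regressing change on arm and baseline gives the same treatment estimate as ANCOVA of the follow-up score. At the implied values baseline correlates about −0.40 with change, so with 94 participants it would pass a p < 0.1 screen about 99% of the time, if it is a candidate. The candidate list may properly sit in the analysis plan. For the secondary questionnaires, the 3-month objectives are framed as covariate-adjusted, and a mixed-model comparison is added, so the point is weaker there. Even so, the primary estimate stays unadjusted, and age group and centre are not assured a place in any model.

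The lower-correlation rows tempt a reader to conclude that the *t* test leaves the trial badly underpowered. The document does not support this. Those rows replace the plan's SD of 10.0; most of that shortfall would be a sample-size matter, and ANCOVA does not restore 80% in either row.

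**Conclusion.** The point holds as one of efficiency, not validity; it does not make the primary result uninterpretable. On the plan's own SD of change, ANCOVA with baseline PAM-13 lowers error variance by about 9-17% and adds roughly 3 to 6 percentage points of power at 5.9 points. It also removes a sensitivity of about −0.23 points per point of chance imbalance. This rests on r of about 0.82, which is derived from the quoted SDs and the assumed 10.0 and is not reported in the article. If the true correlation is lower, the gain is larger, but that is an assumption. The contribution of the strata is expected to be favourable but is unquantified.

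One limit should be stated with the recommendation. Under Procedure (Recruitment), participants are randomised and told their allocation when they receive instructions for the questionnaire tool. Baseline scores may therefore be given with allocation known. A baseline difference caused by that knowledge is not chance, and ANCOVA is not guaranteed to remove it.

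**What to change.** Replace the primary analysis with a linear model of 3-month PAM-13 on arm, baseline PAM-13 (continuous), age group (under 60, 60 and over) and centre, with small centres pooled or centre as a random effect. Report the adjusted mean difference with its 95% CI. State that these covariates are fixed in advance and exempt from the p < 0.1 screen. Keep the *t* test on change as a supportive analysis. Use the same form, with each scale's own baseline, for the EQ-5D-5L, EORTC and HADS comparisons.

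Leave the planned 47 evaluable per group unchanged: with the quoted SDs ANCOVA would need about 40, but that depends on a correlation the article does not report.

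The cost is wording in the protocol and analysis plan. Baseline PAM-13 is already collected and the strata are known at randomisation. The article gives recruitment as pending and says questionnaire responses cannot be viewed until extraction at the end of the study, so the change can be made before outcomes are seen.

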### Primary objective

The primary objective of this study is to test whether the use of OWise increases patient activation scores at 3-month follow-up by at least four points more than standard care.

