### Measures

#### Primary outcome measure

##### Patient Activation Measure (PAM-13)

Patient activation describes the knowledge, skills, and confidence a person has in managing their health and care [23, 24]. The PAM-13 is a 13-item questionnaire that measures patient activation [25]. Each item has four response options from (1) ‘strongly disagree’ to (4) ‘strongly agree,’ and ‘not applicable.’ PAM-13 scores will be calculated according to the guidelines [25]. Scores range on a scale of 1–100 corresponding to four activation levels: 1 (≤ 47.0) not believing activation important, 2 (47.1–55.1) a lack of knowledge and confidence to take action, 3 (55.2–67.0) beginning to take action, and 4 (≥67.1) taking action [25]. This measure has been used widely among cancer patients and across the UK [26–28] and has robust evidence of reliability and validity [23, 29, 30]. Patient activation, as measured by the PAM-13, can be targeted by interventions and change over time [24]. Previous work has shown that higher patient activation is associated with better HRQoL and lower health care utilization [16–18, 31].

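### If triggered, the log-transformation fallback for the primary PAM-13 comparison does not suit a change score or an objective stated in PAM points

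*Protocol article*

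**What the plan says.** All references are to the protocol article.

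- **Primary endpoint**, the test: "We will compare the PAM-13 score change between the intervention arm and the control arm using independent *t* test". The next sentence is "Data will be log-transformed to achieve normality as appropriate". It does not say whether the change or the underlying score would be logged, and it makes the transformation conditional.
- **Primary objective**: the aim is to test whether OWise "increases patient activation scores at 3-month follow-up by at least four points more than standard care".
- **Sample size**: "Sample size calculations are based on the change in PAM-13 score from baseline to 3 months", and "this study is planned to detect a mean change difference of 5.90 assuming a common standard deviation of 10.0".
- **Patient Activation Measure (PAM-13)**: "Scores range on a scale of 1–100 corresponding to four activation levels". A single score is therefore always positive, but a difference between two scores need not be.

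**The concern.** The log sentence directly follows the sentence naming the PAM-13 change as the tested variable, and normality matters for the variable that enters the t test. The change score is therefore its most natural referent, yet a change score takes zero and negative values, for which no log exists. The other available reading, logging raw scores first, avoids undefined values but alters what is estimated. The objective and the sample size are both in PAM points, and a log-scale result is not. If the fallback were used, the primary test would either need an added constant that the article does not fix, or answer a question on a different scale from the one the trial was designed for.

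**Working it through.** **Inputs** (Sample size section)

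- OWise: "the mean PAM-13 score at baseline for the intervention group was 61.3 (SD 16.61) and 67.9 (SD 16.85) at 3 months", so mean change = 67.9 − 61.3 = 6.6.
- Control: "a mean PAM-13 score at baseline of 62.1 (SD 17.30) and 62.8 (SD 14.94) at 3 months", so mean change = 62.8 − 62.1 = 0.7.
- Planning difference = 6.6 − 0.7 = 5.9; SD of change 10.0; two-sided alpha 0.05; power 80%.

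**The plan's own figure.** By the normal approximation, n per arm = 2 × [10 × (1.960 + 0.842) / 5.9]² = 45.1, rounded up to 46. The t-based calculation gives 46.08, rounded up to 47, with 80.8% power at 47 per arm. The stated 47 is reproduced. With attrition, 47 / 0.77 = 61.04, and the plan uses 61. The sizing therefore rests on an untransformed difference in points.

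**Reading 1: log of the change.** Under normality, P(change ≤ 0) = Φ(−mean change / SD).

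- Control: Φ(−0.7/10) = Φ(−0.07) = 47.2%, about 22 of 47.
- OWise: Φ(−6.6/10) = Φ(−0.66) = 25.5%, about 12 of 47.
- 1:1 average: (47.2 + 25.5)/2, about 36.3%, or 34 of 94 evaluable patients.

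Varying the SD of change as an assumption, still under normality, the average is 33.5% at SD 8, 38.4% at SD 12 and 41.1% at SD 16.

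An added constant c restores the log, but the result then depends on c. Since scores run from 1 to 100, the lowest possible change is 1 − 100 = −99, so only c above 99 is safe for every possible value. Evaluated at the two planning means alone, as an illustration, the log contrast is:

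- c = 25: ln(31.6/25.7) = 0.207
- c = 100: ln(106.6/100.7) = 0.057

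The same 5.9-point difference gives log contrasts that differ more than threefold.

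**Reading 2: log of the raw scores, then difference.** ln(3-month score) − ln(baseline score) = ln(3-month score / baseline score). The between-arm contrast is then a ratio of ratios. Four points has no single equivalent on that scale. Taking two of the PAM level boundaries as starting scores:

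- from 47.0: ln(51/47) = 0.082, an 8.5% rise
- from 67.0: ln(71/67) = 0.058, a 6.0% rise

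Neither the four-point objective nor the 5.90-point planning difference can be read off such an estimate.

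**The case against.** The strongest defence is that the sentence is conditional. A log that is undefined for many patients is hardly suitable, so a careful analyst could follow the text and never log a change score. This stands: the plan does not commit to the transformation, and the problem exists only if it is used. But on that defence the sentence either does nothing or sends the analyst to raw scores, where the scale mismatch remains.

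The percentages also assume normality, the condition under which the rule would not be invoked. This stands too. They show that non-positive changes should be expected in number, not how many patients would be affected when the data are skewed.

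A reader might infer that about a third of patients, more of them in control, would be lost from the primary analysis. The article does not support that. It nowhere says that patients without a log would be excluded, and its Analysis section commits to intention-to-treat analysis of everyone randomized.

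A reader might also infer that no result in PAM points would remain. That goes too far. The covariate-adjusted regression in the same section and the mixed model under Secondary endpoints compare mean changes without mentioning a log, although the sentence could be read to cover the regression.

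Finally, a trigger for non-normality, an offset and a back-transformation are details that an analysis plan commonly holds, and their absence here is not the point. The point is that the transformation the article does name fits neither the tested variable nor its objective.

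**Conclusion.** The concern holds as a conditional flaw in the stated rule for the primary endpoint. If the fallback is used on changes, it is undefined for zero and negative values without an arbitrary offset. If it is used on raw scores, it produces a ratio that matches neither the objective nor the sizing. The illustrative share of non-positive changes is 47% in control, 25% in OWise and 36% overall. It rests on the plan's mean changes, SD 10 and normality, and the overall figure moves between 33.5% and 41.1% for SDs from 8 to 16. The scale mismatch under the raw-score reading needs no distributional assumption.

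The planned untransformed t test is not called into question here: its sample size is reproduced and its estimate is on the right scale. Nor does this flaw require replacing that test with an adjusted model, which is a separate matter.

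**What to change.** Delete the log-transformation sentence for the primary endpoint, and state that the primary result is the between-arm difference in mean PAM-13 change, in PAM points. If a fallback for non-normality is wanted, name one that keeps that scale: bootstrap or permutation inference for the mean difference, or robust standard errors. If an analysis plan exists, carry the same wording into it.

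The cost is one sentence. No new data or patients are needed, and the planned 47 evaluable patients per arm and about 80% power are unaffected.
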